### Investigation details

#### CMR

CMR studies will be carried out on a dedicated cardiac research scanner (1.5 Tesla Intera CV, Philips, Best, The Netherlands) equipped with 'Master' gradients (30 mT/m peak gradients and 150 mT/m/ms slew rate) based at the Leeds General Infirmary, Leeds, UK. The CMR signals are received by a 5-element cardiac phased-array coil and ECG gating and triggering will be performed by the vectorcardiographic method. The total scan duration is approximately one hour and will comprise (Fig. 2):

**Figure 2 F2:**
[figure not shown]
**CE-MARC cardiac magnetic resonance protocol**. The protocol commences with a low-resolution survey scan and localisers. Intravenous adenosine is then administered for approximately 4 minutes at 140 mcg/kg/min, following which first pass stress perfusion imaging is undertaken after the injection of 0.05 mmol/kg dimeglumine gadopentetate. Three dimensional whole heart MR coronary angiography follows the low resolution coronary survey and free-breathing 4 chamber cine (used to assess slice coverage and diastolic coronary rest period respectively). Rest perfusion imaging is undertaken a minimum of 15 minutes following stress perfusion, with a further injection of 0.05 mmol/kg dimeglumine gadopentetate. A final injection of 0.1 mmol/kg dimeglumine gadopentetate is given following this sequence, bringing the overall gadolinium dose to 0.2 mmol/kg. Resting left ventricular function is then assessed, initially for three slices planned identically to the perfusion slices, and then for the entire left ventricle using contiguous slices. A modified Look-Locker inversion time scout is performed prior to late gadolinium enhancement imaging in short axis, vertical long axis and horizontal long axis orientations. Times indicated on the diagram are approximate and sequence blocks are not drawn to scale.

1. Low resolution survey and sensitivity encoding (SENSE) reference scans performed prior to the cardiac localiser scans which define short axis, vertical long axis and horizontal long axis acquired with a balanced steady state free precession (SSFP), single slice, breath-hold pulse sequence. Pulse sequence parameters: echo time (TE) 1.6 ms, repetition time (TR) 3.2 ms, slice thickness 8 mm, matrix 192 × 192, field of view 320–400 mm according to patient size, SENSE factor 1.7 to 2.0, 30–50 phases per cardiac cycle.

2. Stress myocardial perfusion study. A T1-weighted saturation-recovery segmented k-space gradient echo pulse sequence combined with SENSE will be used to assess first pass myocardial perfusion in 3 short axis slices, positioned according to the "3 of 5" technique [19]. Pulse sequence parameters: TE 1.0 ms, TR 2.7 ms, flip angle 15°, single saturation pre-pulse per R-R interval shared over three slices, SENSE factor 2, matrix 144 × 144, field of view 320–460 mm, slice thickness 10 mm. For stress perfusion imaging intravenous adenosine will be administered at a dose of 140 μg/kg/min. The patient's blood pressure will be recorded every two minutes and the heart rhythm monitored on the vector-ECG. The perfusion study will commence approximately 4 minutes into the adenosine infusion. A bolus intravenous injection of 0.05 mmol/kg dimeglumine gadopentetate (Magnevist^®^, Schering AG, West Sussex, UK) followed by a 15 ml saline flush will be delivered through an arm vein at 5 ml/s using a power injector (Spectris^®^, Medrad, Pittsburgh, Pennsylvania), while the patient holds their breath in end-expiration.

3. Coronary MR Angiography. A low-resolution coronary survey scan will be performed during free breathing, using a respiratory navigator. Timing of the diastolic coronary rest period is estimated from the four-chamber free breathing cine scan. Three dimensional, whole heart coronary MR angiography is acquired using a balanced SSFP sequence and a respiratory navigator to compensate for respiratory motion during free breathing. Pulse sequence parameters: TE 2.3 ms, TR 4.6 ms, flip angle 100°, T2 and fat saturation pre-pulses, SENSE factor 1.7, duration of acquisition up to 120 ms per R-R interval (determined by length of diastolic rest period), matrix 304 × 304, field of view 320–460 mm, slice thickness 0.9 mm, 100–120 slices as required.

4. Resting myocardial perfusion study. Pulse sequence, slice positioning, and injection characteristics identical to the stress perfusion scan.

5. Additional intravenous injection of dimeglumine gadopentetate (0.1 mmol/kg), given within 60 seconds of the rest perfusion scan, in preparation for late gadolinium enhanced CMR.

6. Resting wall-motion. Contiguous cine stack encompassing the entire left ventricle in 10–12 slices (depending on left ventricular long axis length). Three additional slices, with identical slice positioning to the perfusion sequence will also be acquired. Pulse sequence parameters: balanced SSFP, TE 1.7 ms, TR 3.5 ms, flip angle 60°, SENSE factor 2, matrix 192 × 192, field of view 320–460 mm, slice thickness 10 mm, at least 20 phases per cardiac cycle, 1–2 slices per breath-hold.

7. Late gadolinium enhanced CMR performed between 10 and 20 minutes after step 5. The optimal inversion time to null signal from normal myocardium will be determined using a modified Look-Locker approach [20]. Subsequently, a T1-weighted, segmented inversion-recovery gradient echo sequence will be used to acquire a contiguous stack of short axis slices covering the entire left ventricle. Pulse sequence parameters: non-selective 180° pre-pulse, TE 1.9 ms, TR 4.9 ms, flip angle 15°, inversion time adjusted individually according to the Look-Locker scan, 10–12 short axis slices, single slice per breath-hold, matrix 240 × 240, field of view 320–460 mm as per patient size. Further slices will be acquired in the vertical and horizontal long axis orientations (at least one slice per orientation, more if clinically indicated.)

#### ETT

Exercise tolerance testing will be performed if the patient is able to exercise appropriately. This will take place at the recruiting hospital using standard Bruce protocol in most cases, although alternate protocols can be used if required. The following data will be recorded: Resting heart rate and BP, peak exercise stress heart rate and exercise duration, achievement of 85% age predicted heart rate and total workload (Metabolic Equivalents, METS), reason for test termination including reproduction of clinical symptoms, degree of ST segment shift, presence of arrhythmia and heart rate recovery at one minute.

#### SPECT

SPECT radionuclide imaging will be carried out a dedicated cardiac gamma camera (MEDISO Cardio-C, Budapest, Hungary) based at the Leeds General Infirmary, Leeds, UK. Patients will undergo a two day scanning protocol using the radioisotope tracer 99mTc tetrofosmin (Myoview), standard dose of 400 MBq for each examination, adjusted to weight to a maximum of 600 MBq per examination. Stress and rest ECG gated SPECT images will be acquired with the patients in the supine position with a total of 64 projections, 3 degree interval, every 40 seconds over a 180 degree orbit. At each projection 8 ECG gated frames per cardiac cycle will be acquired. A matrix size of 64 × 64 will be used. Trans-axial stress and rest slices of 6 mm thickness will be reconstructed with a Butterworth scattered back-projection filter, with a cuttoff frequency of 0.4 Nyquist and an order of 6. Transaxial slices will be reorientated to the cardiac axes for analysis. Data will be processed using QGS software (Cedars-Sinai Medical Center, USA) to calculate end diastolic and end systolic volumes and wall motion scores. QPS (Cedars-Sinai Medical Center, USA) will be used to for semiquantitative analysis of the perfusion data including summed stress and rest scores. The stress imaging protocol will be performed using intravenous adenosine (140 mcg/kg/min) for 4 minutes followed by isotope injection so that the perfusion techniques of SPECT and CMR are directly comparable.

#### X-ray Angiography

All patients in this study will undergo invasive X-ray coronary angiography by a cardiologist who will be blinded to SPECT and CMR results. Patient management decisions will be made independently of study participation. The results of CMR will not be routinely available to clinicians. The SPECT results will be made available at the request of the patient's clinician if SPECT was selected as part of the planned investigations had the patient not participated in the trial. Where the SPECT study is performed for study purposes only (and not part of the initial clinical diagnostic pathway) the results may be made available by specific request following the coronary angiogram, to guide patient management for example with regard to identification of inducible ischaemia.

### Annual follow-up

Annual follow-up over the subsequent 3 years will be undertaken. A number of procedural safeguards will be followed to establish survival prior to a follow-up telephone call. Information to be obtained at the telephone consultation includes, medical history since randomisation including details and dates of; acute coronary syndrome, emergency or elective revascularisation procedure, any admission for cardiovascular cause including heart failure, cardiac arrhythmia, suspected cardiac event, acute CHD hospitalisation, stroke/transient ischaemic attack (cerebrovascular). These data will be verified from hospital or family practitioner records. Details of any recent cardiovascular investigations will be taken. In addition, Office of National Statistics (ONS) monitoring will be sought for deceased patients to determine the certified causes of death. Notification of deaths by ONS is independent of the patients' clinical follow-up (if they remain resident in the United Kingdom) and ensures recording of unbiased cause-specific mortality both during the study and after, for an indefinite period.

### Definition of outcomes/events

#### Diagnosis of CHD

Significant CHD will be defined as ≥ 70% stenosis of a first order coronary artery measuring ≥ 2 mm in diameter at X-ray coronary angiography, or left main stem stenosis ≥50%.

#### Major adverse coronary events

To assess the prognostic value of CMR, patients will be followed for three years from test completion for the occurrence of a major adverse coronary event (MACE) which will be a composite endpoint comprising at least one of the following; death from cardiovascular cause, acute coronary syndrome (with clinical and biomarker evidence), late revascularisation (>3 months after the initial coronary angiogram) and hospital admission for any cardiovascular cause.

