### Statistical considerations

#### Sample size

For our primary objective, estimating the diagnostic accuracy of CMR against the reference standard of X-ray angiography we calculated that a sample size of 750 patients would enable us to estimate the sensitivity or specificity of CMR to within +/-3.5%. This assumes a sensitivity (or specificity) of 90% for CMR and 60% prevalence of significant CHD in the study population and is based on the precision of the 95% confidence interval for a proportion. For the secondary objectives of comparing the diagnostic accuracy of CMR with SPECT and also ETT, this number would be sufficient to detect a 6.5% difference in sensitivities (or specificities) between CMR and SPECT with 80% power, assuming a sensitivity of 85% for SPECT and 2-sided analyses at the 5% significance level [22]. As the sensitivity and specificity of ETT is expected to be lower at around 68% sensitivity and 77% specificity, our sample size will provide sufficient power to detect the expected larger differences between CMR and ETT.

To assess the prognostic value of CMR in predicting MACE approximately 10 events are required for each prognostic factor in the statistical model [23]. The prognostic value of the combined CMR conclusion will be assessed after adjusting for the known risk factors age, gender, cholesterol, blood pressure, smoking and diabetes, which would require 70 events. It is estimated that approximately 30% of patients will undergo planned revascularisation based on the angiogram result and for this to be carried out usually within 8 weeks. For the remaining patients we estimate that for every 70 patients, 10 will be normal with an event rate of <1% per year and 60 will have CHD (30 significant and 30 mild) with an event rate of approximately 5% per year. The required sample size of 750 patients for the diagnostic accuracy evaluation would therefore result in approximately 23 patients experiencing an event per year. With a minimum follow-up period of 3 years this would provide the required number of 70 patients with an event.

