#### Prognostic value of CMR (at 3 year follow-up)

The prognostic ability of the combined CMR result alone and after adjusting for the risk factors: age, gender, cholesterol, blood pressure, smoking and diabetes in predicting time to the first major cardiovascular event will be assessed using Cox proportional hazards modelling. Patients not experiencing an event will be treated as censored at their last known follow-up assessment. Hazard ratios and 95% CI will be reported and Kaplan-Meier curves will be calculated. This analysis will be for all patients. Allowing physicians access to SPECT results is ethically unavoidable but may also influence revascularisation decisions and thus introduce an analysis bias. In order to account for any possible bias and any differences in the risk of future events resulting from decisions about revascularization we will conduct additional analyses which will adjust for the impact of revascularization on outcomes by treating it as an intermediate event, using time-dependent covariates and multistate models[24].

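### As written, the cardiovascular-admission component of MACE has no exclusion for revascularisation planned on the index angiogram, which undoes the 3-month rule and conflicts with the 70-event forecast

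*Protocol article*

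**What the plan says.** Under Major adverse coronary events, the protocol article states that "patients will be followed for three years from test completion for the occurrence of a major adverse coronary event (MACE"). Any one component is enough. The last two components are "late revascularisation (>3 months after the initial coronary angiogram) and hospital admission for any cardiovascular cause". The revascularisation component has a time limit. The admission component has no time limit and no exclusion for planned admissions.

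The Sample size section expects that "approximately 30% of patients will undergo planned revascularisation based on the angiogram result and for this to be carried out usually within 8 weeks". It then forecasts events only in the patients who are left. The smaller, low-risk group is described thus: "for every 70 patients, 10 will be normal with an event rate of <1% per year". The larger group, which supplies nearly all the events, is described in these terms: "60 will have CHD (30 significant and 30 mild) with an event rate of approximately 5% per year". From these two groups the section concludes: "The required sample size of 750 patients for the diagnostic accuracy evaluation would therefore result in approximately 23 patients experiencing an event per year", and so about 70 over three years.

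The section on the prognostic value of CMR fits a Cox model for time to first event in all patients. In additional analyses it handles revascularisation by "treating it as an intermediate event, using time-dependent covariates and multistate models". That sentence does not separate early from late procedures.

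The Annual follow-up section collects revascularisation, marked as emergency or elective and with dates, as a separate item from cardiovascular admissions.

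**The concern.** The 3-month limit has an evident purpose. A procedure arranged because of the index angiogram is a consequence of the diagnosis, not a later event that CMR predicts. An admission for planned PCI or bypass surgery at, say, week 6 is nevertheless a hospital admission for a cardiovascular cause, and it falls inside follow-up. Someone classifying events from the definition alone would record it as a first MACE, and the 3-month limit would have no effect for any procedure that involves an admission.

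Three things are at stake.

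- **Meaning of the hazard ratio.** Planned procedures are decided on the angiogram, and the protocol assumes 90% sensitivity or specificity for CMR against that angiogram. A strong association between CMR and these events would largely repeat the primary objective under the name of prognosis.
- **Masking.** Because only the first event counts, a later cardiovascular death or acute coronary syndrome in the same patient would not enter the analysis.
- **The additional analyses.** Where the admission for early revascularisation is already the first MACE, that procedure cannot also be an intermediate step on the way to MACE. Separately, late revascularisation is an endpoint component and also falls under the unqualified term used for the intermediate event, so one procedure could be both state (or covariate) and endpoint.

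**Working it through.** **Inputs from the Sample size section.** 750 patients; 30% with planned revascularisation; the remainder split 10 normal to 60 with CHD in every 70; event rates below 1% and about 5% per year; 3 years of follow-up; "approximately 10 events are required for each prognostic factor in the statistical model", with 7 factors (the CMR result plus six risk factors).

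**Step 1: reproduce the protocol's forecast.**

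- Planned revascularisation: 0.30 × 750 = 225 patients.
- Remaining: 750 − 225 = 525, of whom 525 × 10/70 = 75 are normal and 525 × 60/70 = 450 have CHD.
- Events per year, with the normal rate at its 1% upper bound: 75 × 0.01 + 450 × 0.05 = 0.75 + 22.5 = 23.25.
- Over 3 years: 3 × 23.25 = 69.75.
- Requirement: 7 × 10 = 70.

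The stated 23 per year and 70 in total are recovered, with no events assigned to the 225. The forecast therefore treats planned early revascularisation as a non-event.

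**Step 2: apply the endpoint as worded.** Let f be the share of the 225 planned procedures that involve a countable admission after test completion. The documents do not give f, so it is varied. As in the forecast, the 225 contribute no other events.

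- Planned procedures counted as MACE: 225 × f.
- Share of all first events: 225f / (225f + 69.75).

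| f | Planned procedures counted | All first events | Share |
|---|---|---|---|
| 0 (excluded) | 0 | 69.75 | 0% |
| 0.25 | 56.25 | 126 | 45% |
| 0.50 | 112.5 | 182.25 | 62% |
| 1.00 | 225 | 294.75 | 76% |

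Planned procedures become the majority once 225f exceeds 69.75, that is, once f exceeds 69.75/225 = 0.31.

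**Step 3: sensitivity to the way events are counted.** If patients leave the risk set after a first event, the other events number 75 × (1 − 0.99³) + 450 × (1 − 0.95³) = 66.4. At f = 1 the share is 225/(225 + 66.4) = 77%, so the conclusion does not depend on this choice.

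**The case against.** The best reply is that the protocol plainly did not mean to count these procedures. The specific 3-month limit sits beside the general admission phrase and would be pointless if the general phrase overrode it. The event forecast gives the planned procedures no events. The follow-up section lists revascularisation separately from admissions, and its examples of admissions (heart failure, arrhythmia, suspected cardiac event and the like) are not elective procedures. The prognostic section treats revascularisation as an intermediate event. Read this way, the share is 0%. The article also defers to a later analysis plan, which may define the component.

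The evidence of intent stands, and it rules out a stronger conclusion that a reader might draw: that the endpoint is in fact dominated by planned procedures and that the additional analyses fail. Both depend on the literal reading, and dominance also depends on an admission share that the documents do not give. Procedures done at the angiogram itself or as day cases might not count.

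Intent does not close the gap, however. The problem is not detail left for later but a stated definition that, if followed, gives a result the forecast contradicts. The time-dependent and multistate models are additional, so they do not repair the main all-patient Cox model.

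A reader might also fault the 3-month cut for going by date and not by plan. The documents do not show this to be an error: planned procedures are expected usually within 8 weeks, which leaves a margin, and no figure is given for longer delays. Nor is it a fault that a late procedure and its own admission both qualify, since one episode counts once in a time-to-first-event analysis.

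**Conclusion.** The point holds as a conflict between the endpoint's wording and the protocol's own event forecast. On the literal wording, up to 225 planned procedures could be added to a forecast of about 70 events. Their share of first events could lie anywhere from 0% to about 76%, with a majority above an admission share of about 31%. The size rests on two things: the protocol's 30% expectation and event rates, and the unstated admission share. It is a possible consequence of the wording, not an established feature of the data.

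If the share is large, the Cox hazard ratio for CMR could mostly restate CMR-angiogram agreement. Severity is moderate: this is a secondary objective, and the diagnostic-accuracy analyses do not use MACE.

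**What to change.** - **Major adverse coronary events:** state that the admission component excludes the index angiogram and admissions for elective revascularisation within 3 months of it. The elective or emergency status and the dates already collected at annual follow-up are enough to apply this, so no new data item is needed. Other cardiovascular admissions, elective ones included, can stay in the composite.
- **Prognostic value of CMR:** define the intermediate event as that early revascularisation only, so that late revascularisation is an endpoint and not also a state or time-dependent covariate.
- **Timing:** fix both rules before events are classified for analysis.

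The cost is a small amount of rewording and event classification. Fewer events will be counted than on the literal wording, but the number then agrees with the 70 on which the prognostic model was sized.

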### Statistical considerations

#### Sample size

For our primary objective, estimating the diagnostic accuracy of CMR against the reference standard of X-ray angiography we calculated that a sample size of 750 patients would enable us to estimate the sensitivity or specificity of CMR to within +/-3.5%. This assumes a sensitivity (or specificity) of 90% for CMR and 60% prevalence of significant CHD in the study population and is based on the precision of the 95% confidence interval for a proportion. For the secondary objectives of comparing the diagnostic accuracy of CMR with SPECT and also ETT, this number would be sufficient to detect a 6.5% difference in sensitivities (or specificities) between CMR and SPECT with 80% power, assuming a sensitivity of 85% for SPECT and 2-sided analyses at the 5% significance level [22]. As the sensitivity and specificity of ETT is expected to be lower at around 68% sensitivity and 77% specificity, our sample size will provide sufficient power to detect the expected larger differences between CMR and ETT.

To assess the prognostic value of CMR in predicting MACE approximately 10 events are required for each prognostic factor in the statistical model [23]. The prognostic value of the combined CMR conclusion will be assessed after adjusting for the known risk factors age, gender, cholesterol, blood pressure, smoking and diabetes, which would require 70 events. It is estimated that approximately 30% of patients will undergo planned revascularisation based on the angiogram result and for this to be carried out usually within 8 weeks. For the remaining patients we estimate that for every 70 patients, 10 will be normal with an event rate of <1% per year and 60 will have CHD (30 significant and 30 mild) with an event rate of approximately 5% per year. The required sample size of 750 patients for the diagnostic accuracy evaluation would therefore result in approximately 23 patients experiencing an event per year. With a minimum follow-up period of 3 years this would provide the required number of 70 patients with an event.

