## Background

Coronary heart disease (CHD) is a major cause of morbidity and mortality in the UK, affecting approximately 2.6 million people [1]. In a typical hospital setting, a variety of investigations may be used to diagnose CHD, risk stratify patients and plan their clinical management. The highest risk patients may proceed directly to X-ray coronary angiography, but the vast majority of patients at low to intermediate risk undergo non-invasive assessment in the form of exercise tolerance testing (ETT), stress echocardiography or single photon emission computed tomography (SPECT), in order to identify those most likely to require coronary revascularisation. The diagnostic process commonly involves a multiple-test strategy, either due to limitations in the performance of any individual test (e.g. ~30% of patients may be physically unable to perform an adequate ETT) or limitations in the test's diagnostic accuracy. For example, the reported sensitivity and specificity of ETT for angiography-proven CHD was 68% and 77% respectively from a large meta-analysis where the prevalence of CHD was high at over 60% [2]. SPECT provides greater diagnostic accuracy than ETT, 86% and 74% sensitivity and specificity respectively, compared to X-ray angiography for the diagnosis of CHD [3], being typically performed in patients with equivocal ETT results, those who cannot exercise or those who have fixed resting ECG abnormalities such as left bundle branch block [3].

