### Secondary objectives

#### Comparison of CMR with SPECT and ETT

The sensitivity, specificity, positive and negative predictive values and corresponding 95% confidence intervals for the diagnostic performance of SPECT and ETT compared with the X-ray angiogram will be calculated. For the comparison of CMR with SPECT and also with ETT we will use McNemar's test to compare the sensitivities and specificities.

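### One 80% power claim covers both sensitivity (450 patients) and specificity (300 patients); it is met for sensitivity, but for specificity it depends on a SPECT rate and a discordance that are not stated

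*Protocol article*

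**What the plan says.** The protocol article, under Sample size, fixes 750 patients from the precision of the primary analysis: "a sample size of 750 patients would enable us to estimate the sensitivity or specificity of CMR to within +/-3.5" percent, with CMR sensitivity or specificity taken as 90% and "60% prevalence of significant CHD in the study population". It then makes a single power statement for the secondary comparison: "sufficient to detect a 6.5% difference in sensitivities (or specificities) between CMR and SPECT with 80% power, assuming a sensitivity of 85% for SPECT". The test level given there is two-sided 5%. No SPECT specificity, discordant proportion or within-patient correlation accompanies it. The method is referred to a cited source.

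The section on the comparison of CMR with SPECT and ETT sets the test: "we will use McNemar's test to compare the sensitivities and specificities". The Background gives published SPECT accuracy as "86% and 74% sensitivity and specificity respectively, compared to X-ray angiography", and a combined CMR sensitivity and specificity of 96% and 83%.

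**The concern.** Sensitivity is estimated in patients with significant CHD and specificity in those without. At 60% prevalence these groups are unequal, so one detectable difference with one power figure cannot describe both unless the inputs differ in a compensating way. The statement also supplies a SPECT rate for sensitivity only, while the one SPECT specificity in the document is 11 points lower. A rate nearer 50% has more variance, so the same 6.5-point difference is harder to detect.

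Comparing CMR with SPECT is a named secondary objective. If the specificity comparison comes out non-significant, a reader relying on this paragraph would take it as an 80%-powered result for 6.5 points. The document does not show that it is.

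**Working it through.** **Inputs.** N = 750, prevalence 60%, difference d = 0.065, SPECT 85%, two-sided 5% (Sample size); McNemar's test (comparison section); SPECT specificity 74% and CMR specificity 83% (Background); CMR 90% (Sample size). CMR is taken as the better test. Discordance is not given, so it is varied.

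**Denominators.** 750 × 0.60 = 450 with CHD; 750 × 0.40 = 300 without.

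**Formulas.** With rates p1 (CMR) and p2 (SPECT) and within-patient correlation ρ among patients of the same disease status, the discordant proportion is

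ψ = p1(1 − p2) + p2(1 − p1) − 2ρ√[p1(1 − p1)p2(1 − p2)]

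and McNemar power is approximately

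Φ{[d√n − 1.96√ψ] / √(ψ − d²)}.

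**The plan's own figure, sensitivity (n = 450, 85% v 91.5%).**
- Independence: ψ = 0.915 × 0.15 + 0.85 × 0.085 = 0.2095. Power = Φ[(1.379 − 0.897)/0.453] = 85.6%.
- Largest possible discordance: ψ = 0.15 + 0.085 = 0.235. Power = 81.4%.
- So 80% is met as a lower bound. The difference detectable at exactly 80% under independence is 6.1 points.

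**Specificity (n = 300).**
- 85% v 91.5%, independence: Φ[(1.126 − 0.897)/0.453] = 69.3%.
- 74% v 80.5%, independence: ψ = 0.805 × 0.26 + 0.74 × 0.195 = 0.3536. Power = Φ[(1.126 − 1.166)/0.591] = 47.3%.

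Other forms of the calculation (unpooled variance, conditional, summed binomial with and without continuity correction, unpaired) give 65% to 70% for the first and 43% to 48% for the second.

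**Effect of positive correlation, n = 300, d = 6.5 points.**

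| ρ | SPECT 85% | SPECT 74% |
|---|---|---|
| 0 | 69.3% | 47.3% |
| 0.1 | 73.7% | 51.4% |
| 0.2 | 78.3% | 56.1% |
| 0.3 | 83.2% | 61.7% |
| 0.5 | 92.8% | 75.9% |

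Power of 80% requires ψ of at most 0.163. That corresponds to ρ of about 0.235 at SPECT 85% and about 0.55 at SPECT 74%.

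**Detectable difference at 80% power, n = 300.**

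| SPECT specificity | ρ = 0 | ρ = 0.3 |
|---|---|---|
| 85% | 7.3 points | 6.3 points |
| 74% | 9.4 points | 8.0 points |

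**Differences implied by the document's own CMR specificities, against SPECT 74%, n = 300, independence.**
- CMR 83% (9 points): ψ = 0.3416, power 76.3%.
- CMR 90% (16 points): ψ = 0.308, power 99.9%.

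**The case against.** The best reply is that the figure may have been worked out on the 300 patients after all. The stated precision supports this: 1.96√(0.9 × 0.1/300) = 3.4%, close to 3.5%, whereas 450 patients would give 2.8%. At 85%, a correlation of about 0.235 yields exactly 80% with 300 patients, while 450 patients exceed 80% at every possible discordance. Positive dependence is also plausible, since the SPECT section says the stress protocol was chosen to make the two perfusion techniques comparable. All of this stands. A reader might infer that 6.5 points was computed for sensitivity and extended to specificity by oversight; the documents do not show that. They equally do not state the 85% specificity or the discordance that the claim would need.

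A reader might also infer that the specificity comparison is underpowered. The 47% holds the difference at 6.5 points, which puts CMR at 80.5%, a value found nowhere in the document. On its cited rates the expected difference from 74% is larger, and power is 76% or more.

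Two further inferences fail. Setting CMR at 90% against SPECT at 85% suggests the trial should be sized for 5 points, but the 90% is the precision assumption for the primary objective and 6.5 points is a detectable difference, so they do not conflict. The ETT sentence, "As the sensitivity and specificity of ETT is expected to be lower at around 68% sensitivity and 77% specificity", reads naturally as lower than CMR, so the cited SPECT specificity of 74% does not contradict it. If about 30% cannot exercise, 300 × 0.70 = 210 patients inform that comparison, and 90% v 77% still has 95% power under independence. At most, its adequacy for specificity assumes CMR near 90% among those able to exercise; at the cited 83% power would be 33%.

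**Conclusion.** The point holds in limited form. The single power statement is supported for sensitivity (about 86%, never below 81%, with CMR at 91.5%). For specificity it is not shown to hold. At a SPECT specificity of 85%, power runs from 69% under independence to 80% or more once discordance is about 16% or lower. At 74%, the only SPECT specificity in the document, power for 6.5 points is 47% under independence and 62% at a correlation of 0.3, and it stays below 80% until about 0.55.

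These figures rest on 60% prevalence, complete data on both tests, CMR being the better test, and the normal approximation to McNemar power. The defect lies in what the design is said to deliver. The number of patients and the primary precision claim are not in question.

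**What to change.** State the two comparisons separately under Sample size:

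- **Sensitivity (450 patients):** 6.5 points from a SPECT sensitivity of 85%, with at least 80% power.
- **Specificity (300 patients):** the difference detectable with 80% power, with its assumed SPECT specificity and discordance. Examples are about 7.3 points at 85% or 9.4 points at 74% under independence, and about 6.3 and 8.0 points at a correlation of 0.3.

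The parenthetical mention of specificities can stay on the 6.5-point claim only if a SPECT specificity of 85% and a discordance of at most about 16% are written down as assumptions. Optionally, add to the ETT sentence that the specificity comparison assumes CMR near 90% among those able to exercise.

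The cost is a few sentences. No patients, procedures or analyses change, although the stated detectable difference for specificity may become less favourable.
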